## Abstract

**Background:**

The prevalence of diabetes is rising in older people. In 2018, over 574,000 Australians reported having diabetes. The highest prevalence (19.4%) of diabetes has been observed in people aged 85 years and older. Clinical guidelines recommend that diabetes management should be individualized; however, there is limited information regarding the current management patterns of diabetes in older people, given most clinical trials exclude participants from this age group. Available data identify that few individuals achieve optimal glycemic levels in the general population, potentially leading to adverse health outcomes and impact on quality of life. The data on glycemic profiles of older population are limited.

**Objective:**

The aim of this study is to examine individualized diabetes management intervention for older people through home visits with a credentialed diabetes educator (CDE) and telehealth consultations with an endocrinologist located at a tertiary hospital.

**Methods:**

This paper describes the design and methodology of a mixed methods feasibility and safety study to identify the current management of type 2 diabetes in people aged 65 years or older. We will implement and evaluate a personalized approach to management in the community of an Australian metropolitan city. This management approach will utilize flash glucose monitoring and home visits with the support of a community home nursing service CDE and telehealth consultation with an endocrinologist located at a local tertiary hospital.

**Results:**

The study commenced in February 2017 and has recruited 43 participants, with final data collection to be completed by July 2019. Data analysis will commence after final data collection, with results expected to be published by the end of 2019.

**Conclusions:**

This study is the first of its kind to explore individualized diabetes management for community-dwelling older people, with an aim to achieve optimal glycemic levels (glycated hemoglobin between 53 and 69 mmol/mol [7%-8.5%] depending on the fitness and frailness of the older individual). The data drawn from this study may be used to inform policy makers, service providers, clinicians, and older adults living with diabetes.

**International Registered Report Identifier (IRRID):**

DERR1-10.2196/13986

## Introduction

The prevalence of type 2 diabetes in older Australians is increasing. In 2015, 1 in 6 Australians aged 65 years or older reported living with diabetes [1]; the incidence of this disease peaks between the ages of 65 and 74 years [2]. Diabetes care is particularly challenging in older adults because of the longer duration of the disease and the increased likelihood of complications, comorbidities, falls, and polypharmacy [3]. In addition, there is a lack of an evidence base regarding the safety and efficacy of diabetes pharmacotherapy in this population.

International guidelines recommend that diabetes care and glycemic targets should be individualized with consideration of the patient’s age, comorbidities, functional status, and living situation [4,5]. In particular, treatment of hyperglycemia should be carefully balanced with the avoidance or minimization of hypoglycemia [6]. This is often difficult in older individuals with long durations of diabetes and possible underlying secondary pancreatic failure.

Currently in Australia, health care delivery of diabetes management in older adults is conducted through primary care or hospital-based diabetes clinics. These environments are not necessarily ideal, as they do not easily allow assessments of home situations and true functional status [7]. An alternative approach is telemedicine, defined by the American Telemedicine Association as the use of medical information exchanged from one site to another via electronic communications to improve a patient’s clinical health status. Telemedicine has been successfully used for the management of chronic diseases in this age group [8]. The current approach involves the credentialed diabetes educator (CDE) using their laptop to link into Web videoconferencing in the home of the person living with diabetes to link with the endocrinologist located in the hospital for joint initial and final review appointments. This approach has been used effectively previously, with good acceptability [9].

We hypothesize that a specialist-led telemedicine service, including flash glucose monitoring technology, is a safe and feasible method of delivering diabetes care to older Australians in Melbourne, Victoria. This study is the first of its kind to trial individualized diabetes management plans for older people through home visits with a CDE and telehealth consultations with an endocrinologist located at a tertiary hospital [10].

## Methods

This protocol paper structure is per the Standard Protocol Items for Clinical Trials guidelines [11].

### Study Design and Setting

This is a feasibility and safety trial, using Simon’s 2-stage design [12], of a new model of health care. This study will use a mixed methods approach describing quantitative glycemic data and qualitative interviews regarding person-centered outcomes.

The study will include older individuals, aged 65 years or older, living with type 2 diabetes, and residing in the northern region of metropolitan Melbourne. The Older People with Type 2 diabetes—Individualizing Management wIth SpecializEd (OPTIMISE) team delivering care consists of the following: (1) a CDE working with a home service organization providing home visits and (2) an endocrinologist based at the tertiary teaching hospital. Joint telehealth consultations will be conducted with the endocrinologist at the hospital and the CDE with participants with diabetes in the participants’ home, including the use of flash glucose monitoring data collected by participants in the preceding 2 weeks to inform clinical decision making.

### Aim

The primary aim is to trial the safety and feasibility of a new model of diabetes care, aimed to optimize diabetes management and improve quality of life at home using a specialized OPTIMISE community team.

The secondary aims are as follows:

To describe the current diabetes managementTo trial the effectiveness of a specialized community-based team to optimize diabetes management and improve quality of life of older people with type 2 diabetes.

### Primary Research Questions

The primary research questions are as follows:

Among community-dwelling older adults with type 2 diabetes, is the OPTIMISE model of care safe?Among community-dwelling older adults with type 2 diabetes, is the OPTIMISE model of care feasible?

The OPTIMISE model will be deemed safe if all the following conditions are met:

There are no deaths associated with diabetes intervention.There are no serious adverse events causally related to the intervention as adjudicated by a panel of physicians within 1 week of the event.The participant spends <30% of time in severe hyperglycemia (>20 mmol/L) measured by flash glucose monitoring, andThe participant spends <5% of time in hypoglycemia (<4 mmol/L) measured by flash glucose monitoring.

The OPTIMISE model will be deemed as feasible if the following conditions are met:

The approached participant agrees to proceed with the intervention at the first visit by the CDE.The participant completes the 4-month intervention by supplying a flash glucose monitor data capture rate of at least 40% (defined as the number of 15-min time points with glucose values captured divided by the total number of 15-min time points for the duration the sensor was applied); 40% was chosen as the feasibility value as previous larger clinical trials involving younger participants with type 1 and 2 diabetes have accepted 50% as clinically sufficient data [13,14].The participant attends at least 80% of scheduled follow-up appointments.

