At the end of the trial, the CDE and endocrinologist will be invited to participate in a face-to-face interview, which will be audio-taped and transcribed, to ascertain their experiences of providing care to participants. The interview will start with an open question asking them to describe their experiences of the care they provided as part of the team. Prompts will be used, if needed, to ensure inclusion of the following pivotal information: their satisfaction with their role in the team; their experiences of working with the endocrinologist or CDE; their experiences of using the flash glucose monitor; the experience of using telehealth, including the performance of telehealth such as connectivity; whether they encountered safety concerns during the study; what are their thoughts about the impact of this program on the participants with diabetes; what they thought could have been improved and what worked well in the care delivery; and if the program were to be run as business as usual at their organization, whether they would want to be a part of the team.

The intervention will be deemed as both feasible and safe, worthy of further investigation in a subsequent randomized comparative trial, if it proceeds to the second phase of Simon’s 2-stage design [12] and more than 31 out of 43 participants do not experience feasibility or safety issues.

To evaluate the impact of the program on participants, secondary outcome measures will be collected, including: biochemical markers, person-centered measures, and service data (shown in Multimedia Appendix 2 [21-25]).

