### Sample Size

Simon’s 2-stage design is used where a group of participants is enrolled in the first stage, and depending on the successful outcome of this group, a second group of participants is then enrolled [12]. In the first stage, 11 participants will be recruited. If 7 or more participants do not experience feasibility or safety issues, the study will proceed to phase 2, where 32 additional participants are recruited for a total of 43. The study design yields a type 1 error rate of 0.05 and power of 0.8 when the true proportion of patients without a negative composite feasibility/safety outcome is 0.8.

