### Statistical Methods/Analysis

Baseline clinical, social, demographic, and biochemical data will be presented as counts (proportions), means (SDs), or medians (interquartile ranges), depending on the nature of the underlying distribution. The proportions of patients with specific outcomes will be reported with corresponding 95% CIs.

If more than 31 out of 43 participants do not experience feasibility or safety issues, the intervention will be deemed worthy of further investigation in a subsequent randomized comparative trial.

Statistical analysis will be undertaken by STATA (ICv 14) software (StataCorp, College Station, TX).

Interviews with participants will be analyzed thematically using a constant comparative approach [26]. Transcripts will be read by researchers, emergent themes discussed, and interpretations compared.

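### The protocol gives two unreconciled rules for deeming the model safe: no related deaths or serious adverse events at all, or at least 32 of 43 participants free of any issue

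*Protocol article*

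**What the plan says.** The first primary research question asks whether the model of care is safe. Under Primary Research Questions the answer is introduced by "The OPTIMISE model will be deemed safe if all the following conditions are met". Four conditions follow. Two are worded for the study as a whole: "There are no deaths associated with diabetes intervention" and "There are no serious adverse events causally related to the intervention as adjudicated by a panel of physicians within 1 week of the event". The other two are limits on the time a participant spends in severe hyperglycemia and in hypoglycemia, worded per participant. The feasibility conditions that follow are also worded per participant.

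Follow-Up Assessments gives a verdict on the same question: "The intervention will be deemed as both feasible and safe, worthy of further investigation in a subsequent randomized comparative trial", provided the study reaches the second stage and "more than 31 out of 43 participants do not experience feasibility or safety issues".

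Statistical Methods/Analysis repeats the threshold with a narrower conclusion: "If more than 31 out of 43 participants do not experience feasibility or safety issues, the intervention will be deemed worthy of further investigation". It does not use the word safe.

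Sample Size sets the two stages (11 participants, continue if 7 or more are issue-free, then 32 more for a total of 43). It quotes a type 1 error of 0.05 and a power of 0.8 for a true proportion of 0.8 without a negative composite feasibility/safety outcome. None of the last three sections contains an overriding condition on deaths or related serious adverse events.

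**The concern.** Two sections say when the model is deemed safe, and they use different criteria. Read as written, the first lets a single related death or related serious adverse event settle the question against the model. The second counts that event as one failed participant, with the same weight as attendance below 80%, and still allows a verdict of feasible and safe if enough others are issue-free.

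The list in Primary Research Questions also mixes two units, the study and the participant, and the protocol does not say how they combine. If the choice is left open until the data are seen, the answer to a primary question depends on which section is applied. That answer is also the stated gate to a randomized trial. The quoted power belongs to the participant count, so it would not describe a verdict that also required zero related events.

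**Working it through.** **Inputs from the protocol.** Stage 1: 11 participants, go if at least 7 are issue-free. Total 43. Success if more than 31, that is at least 32, are issue-free. Design alternative 0.8. The null proportion is not stated.

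**Failures allowed by each rule.** The count rule allows 43 − 32 = 11 participants with an issue of any kind (11/43 = 25.6%). The zero-event conditions allow 0 related deaths or serious adverse events. With 1 to 11 affected participants the verdicts can differ.

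**The plan's own power figure.** For a true issue-free proportion p,

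P(pass) = Σ over x = 7 to 11 of P(Bin(11, p) = x) × P(Bin(32, p) ≥ 32 − x).

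At p = 0.80 this is 0.840, not the stated 0.80. At an assumed null of 0.6 the type 1 error is 0.033 rather than 0.05. This mismatch is a separate matter and the present point does not depend on it, but it is why 0.84 is the baseline below.

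**Adding the zero-event conditions.** Let q be a participant's probability of a related death or related serious adverse event. The protocol gives no value, so q = 0.5%, 1% and 2% are assumptions. Take participants as independent, hold p at 0.80, and treat each such event as one of the composite failures (other failures then have probability 0.20 − q). Then

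- P(no related event in 43) = (1 − q)^43;
- given no related event, a participant is issue-free with probability 0.80/(1 − q);
- P(both rules met) = (1 − q)^43 × P(pass at 0.80/(1 − q));
- P(count rule passes, zero-event conditions fail) = 0.840 − P(both rules met).

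| q (assumed) | (1 − q)^43 | 0.80/(1 − q) | P(pass) at that value | Both rules met | Count passes, zero-event fails |
|---|---|---|---|---|---|
| 0.5% | 0.806 | 0.804 | 0.855 | 0.69 | 0.15 |
| 1% | 0.649 | 0.808 | 0.870 | 0.56 | 0.28 |
| 2% | 0.420 | 0.816 | 0.896 | 0.38 | 0.46 |

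**What zero events would show.** With 0 related events in 43, the exact one-sided 95% upper bound for the event probability is 1 − 0.05^(1/43) = 6.7%.

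**The case against.** The strongest reply is that there is only one rule. Sample Size speaks of a composite feasibility/safety outcome per patient. On that reading Primary Research Questions lists the components, and the later sections count the participants free of all of them. Five of the seven safety and feasibility conditions are worded per participant; only the death and serious-event conditions are not. The defect would then be loose wording of two conditions.

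This reading is coherent and may be what was meant, but the text does not settle it. The lead sentence is about the model, and the two conditions say that there are no such events. If the composite was intended, Primary Research Questions states the safety criterion wrongly. If a study-level condition was intended, the other sections omit it. Either way some text has to change.

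Other parts of the reply stand and limit the point:

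- Statistical Methods/Analysis concludes only that further investigation is warranted, so the direct conflict is between Primary Research Questions and Follow-Up Assessments.
- Proportions with specific outcomes are already to be reported with 95% confidence intervals, and both ethics committees are to be told of major adverse events on the same day. A related death would not go unseen. Neither provision says how such an event bears on the verdict.
- The study is a small feasibility trial whose positive outcome is a recommendation for a randomized trial, not a final claim of safety.

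**Conclusion.** The point holds as an unreconciled decision rule for the primary safety question. The existence of the conflict needs no assumption; it follows from the wording of the two sections and the count 43 − 32 = 11. Its size does rest on assumptions: an issue-free proportion of 0.80, independent participants, and related-event rates that the protocol does not give. At 0.5%, 1% and 2%, the chance of opposite verdicts is about 0.15, 0.28 and 0.46.

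A reader might infer more than the document supports:

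- That the plan accepts 11 related deaths or serious events. Eleven is the ceiling on a composite shared with glucose, data-capture and attendance failures; it would be reached only if every failure were a related event.
- That all 43 participants must meet every condition, so that success is nearly impossible (0.8^43, below 0.0001). This takes the conditions on the participant to mean every participant, the least plausible reading.
- That the two rules cannot be reconciled. The per-participant reading shows that they can be; the protocol has not done it.

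**What to change.** Before analysis, reconcile Primary Research Questions, Follow-Up Assessments, Sample Size and Statistical Methods/Analysis into one rule. State whether related deaths and related serious adverse events are (a) a study-level condition in addition to the 32/43 count, or (b) individual failures within the composite only. The document does not show which was intended, so the authors must say.

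- Under (a), state that the power in Sample Size describes the composite count only and that power for the joint verdict is lower: about 0.69, 0.56 and 0.38 at the assumed rates, against 0.84 for the count rule as written.
- Under (b), reword the two conditions in Primary Research Questions per participant, and do not describe 32/43 alone as showing that the model is safe.
- In either case, report safety failures and feasibility failures separately, and give the number of related deaths and serious events with an exact upper confidence bound.

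The change should be a dated, disclosed amendment. The Results section says that 43 participants have consented, and in this single-arm study the diabetes educator asks about adverse events monthly, so some events may already be known when the rule is fixed.

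No new data are needed. The cost is the amendment itself and, if (a) is chosen, a less favorable power figure for the joint verdict.

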### Recruitment

Participants with type 2 diabetes will be recruited from several sources, which are as follows:

Existing home nursing clients: the CDE will screen and identify eligible participants from the Northern site of the home nursing organization.Tertiary hospital: the endocrinologist will screen new referrals to the diabetes clinic.Tertiary hospital: the endocrinologist will screen all recently admitted inpatients with glycated hemoglobin (HbA_1c_) level of greater than or equal to 6.5%.Referrals from other clinicians in the region: diabetes educators, geriatricians, and general practitioners who have working relationships with the research team will be invited to refer eligible participants.Self-referrals from the community who meet eligibility criteria.

Once identified, the CDE will contact potential participants to inform them of the study. If interested, the first home visit will be arranged to explain the study and answer questions. If the participant agrees to proceed, a second home visit is organized to discuss the participant information and consent form and obtain informed consent.

Health care providers involved in the OPTIMISE team will be invited to participate, provided with the participant information and consent form, and given the opportunity to ask questions.

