### Baseline Clinical Data Assessments

Once recruited, the CDE will organize a third home visit with the participant for baseline data collection; the details are shown in Table 1.

**Table 1 table1:** Older people with type 2 diabetes individualizing management with specialized baseline participant and biochemistry data collection.

Baseline participant information components	Content of the baseline participant information
Demographic data	Age, gender, country of birth, language(s) spoken, education level, and socioeconomic index for areas
Descriptive data	Height, weight, blood pressure, medical history, medical diagnoses, medication names, doses and directions of use, and history of falls in the past 12 months
Mini Nutritional Assessment-Short Form [15]	Nutrition
Rowland Universal Dementia Assessment Scale [16]	Dementia or Cognitive Impairment: The Rowland Universal Dementia Assessment Scale
Charlson Comorbidity Index [17]	Prognostic comorbidity for mortality
Diabetes-specific information	Duration of diabetes, family history, current pharmacotherapy, relevant comorbidities, hypoglycemia, and hyperglycemia risk
Biochemistry data collection	Glycated hemoglobin, Liver function tests, lipid profile, fasting plasma glucose, renal function, full blood examination, and spot urinary albumin to creatinine ratio

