## Results

The project was funded in November 2016 and approved by the respective organizations (as noted above) in February 2017. Data collection commenced in July 2017, with anticipated data collection to cease in July 2019; 43 participants have consented to participate, with data analysis to commence after final data collection is complete. We anticipate results to be published by the end of 2019.

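### Agreement at the first visit is a feasibility condition that every counted participant meets by construction, so the feasibility verdict says nothing about uptake

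*Protocol article*

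**What the plan says.** Under Primary Research Questions, the protocol article lists three feasibility conditions. The first is "The approached participant agrees to proceed with the intervention at the first visit by the CDE". The second is sensor data capture of at least 40%, and the third is attendance at 80% or more of booked follow-up visits.

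The route into the study is given under Recruitment. After a contact by the CDE, "If interested, the first home visit will be arranged to explain the study and answer questions". Then "If the participant agrees to proceed, a second home visit is organized to discuss the participant information and consent form and obtain informed consent". Baseline Clinical Data Assessments continues the sequence: "Once recruited, the CDE will organize a third home visit with the participant for baseline data collection".

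The decision rule is given under Sample Size and Statistical Methods/Analysis. "In the first stage, 11 participants will be recruited", and then "If 7 or more participants do not experience feasibility or safety issues, the study will proceed to phase 2, where 32 additional participants are recruited". The final criterion is "If more than 31 out of 43 participants do not experience feasibility or safety issues, the intervention will be deemed worthy of further investigation". Follow-Up Assessments repeats that criterion as the test for calling the intervention both feasible and safe. Results reports that "43 participants have consented to participate".

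**The concern.** Agreement to proceed describes everyone who is offered the programme, including those who say no. The verdict is counted only over people who said yes and then consented. One of the three stated feasibility conditions is therefore inert in the count that decides the trial.

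Feasibility is one of the two primary questions, and the verdict is meant to inform whether a randomised trial is worth pursuing. Willingness to take part bears directly on whether such a trial could recruit. A reader who sees agreement listed as a condition, and then sees the threshold of 43 passed, would reasonably think that uptake had been tested. It would not have been.

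**Working it through.** **Step 1: who can be counted.** The article's own sequence is:

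| Stage | Section | Who remains |
|---|---|---|
| Contact by the CDE | Recruitment | Those interested go on to a first visit |
| First home visit | Recruitment | Those who agree go on to a second visit |
| Second home visit | Recruitment | Those who consent |
| Third home visit | Baseline Clinical Data Assessments | Those already recruited |
| Counted in the rule | Sample Size; Statistical Methods/Analysis | 11 recruited, then 11 + 32 = 43 recruited |

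A person who refuses at the first visit leaves two steps before being counted. Hence P(first condition fails, given recruited) = 0, and the condition adds no failures to the 11 or the 43.

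**Step 2: the alternative denominator.** If the rule were meant to count everyone approached, 11 and 43 would be numbers of approached people. Sample Size calls them recruited, and Results says that the 43 have consented. That reading does not fit.

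**Step 3: what the rule cannot see.** The number of people needed at the first visit to yield 43 who agree is 43 divided by uptake, rounded up. For simplicity this ignores losses between agreement and consent. It gives 48 at 90% (43/0.9 = 47.8), 54 at 80% (53.75), 62 at 70% (61.4) and 86 at 50%. These uptakes are assumptions. The rule applied to the 43 is identical in each case.

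**Step 4: the plan's own operating figures.** For success probability p, the written rule gives

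P(positive) = sum over x = 7 to 11 of C(11,x) p^x (1−p)^(11−x) × P(Bin(32,p) ≥ 32 − x).

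At p = 0.8 this is 0.840, against the stated power of 0.8. The null proportion is not stated. At an assumed 0.6 the type 1 error is 0.033, and over 0.5 to 0.65 it runs from 0.0009 to 0.119. The stated figures are therefore not exactly reproduced, but that is a separate matter and nothing here depends on it.

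**Step 5: illustration of scale.** Keep the written rule, but count people who received a first visit and treat refusal as failure. Then p = uptake × success among enrolled participants.

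| Uptake (assumed) | p if enrolled succeed at 0.8 | P(positive) | p if enrolled succeed at 0.9 | P(positive) |
|---|---|---|---|---|
| 100% | 0.80 | 0.84 | 0.90 | 0.997 |
| 90% | 0.72 | 0.41 | 0.81 | 0.88 |
| 80% | 0.64 | 0.09 | 0.72 | 0.41 |

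On the recruited denominator the probability stays at 0.84 (or 0.997) in every row.

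**The case against.** **A later refusal.** The first condition speaks of agreeing to the intervention, while the first visit under Recruitment explains the study. The condition might therefore catch someone who consents and then declines to start. The participant flowchart (Multimedia Appendix 1), which might settle this, is not shown. This reading is possible but strained. The condition refers to a person being approached and to the first CDE visit, and under Recruitment that visit comes before consent.

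**The illustration.** The documents give no uptake. First visits are arranged only for people who have already expressed interest, so agreement at that point could be high. Sample Size defines 0.8 for the whole composite; on an approached denominator it would already include refusal, and multiplying it by uptake lowers it a second time. The denominator in the illustration is also not one that the article uses or that the remedy proposes. All of this stands, so the figures show sensitivity only and do not measure an error in the trial.

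**Reporting of uptake.** Statistical Methods/Analysis promises proportions with 95% CIs for specific outcomes, and service data are collected under Multimedia Appendix 2. Uptake may therefore be reported. That also stands: the gap is that uptake has no role in the verdict, not that it will go unreported.

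**Conclusion.** The point holds on the article's own text. The first feasibility condition is satisfied by all 11 and all 43 counted participants, so refusal at the first visit cannot move either the 7-of-11 or the more-than-31-of-43 decision. It could act only indirectly, by stopping recruitment short, and Results shows that 43 was reached. The conclusion rests on reading the first CDE visit in the condition as the first home visit under Recruitment.

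A reader might infer more than this, and three stronger readings are not supported:

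- **That the composite is void.** Data capture, attendance and the four safety conditions can all still fail.
- **That a model most older people decline would be sent to a randomised trial.** The documents do not say how many declined, and the article commits only to calling the intervention worth investigating further.
- **That uptake of 93% is required.** This comes from (32/43)/0.80 = 0.744/0.80 = 0.93, which treats an expected proportion as a hard limit. The illustration gives a 0.41 chance of success at 90% uptake.

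**What to change.** Take the first condition out of the participant-level composite. Report uptake as a separate feasibility criterion: the number agreeing at the first visit divided by all people who received a first visit, with a 95% CI. Report refusals at the earlier contact stage separately where they were recorded, since they are not what the stated condition describes. Make the conclusion of feasibility depend on both the composite and uptake.

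All 43 had already consented, so a minimum uptake can no longer be pre-specified in the ordinary sense. Any minimum should be set without sight of the refusal counts and labelled as added after enrolment. If that is not possible, restate the more-than-31-of-43 verdict as feasibility among people who had already agreed to take part.

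The cost is a change of wording and a count from contact records, with no new participants. The count depends on those records having been kept, and the article does not describe a log of approaches or refusals. The feasibility result may also look less favourable.
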